**Methods/Design:**

A randomized, controlled, double-blind, clinical trial will be carried out involving 85 male and female adolescents between 15 and 18 years of age. The research diagnostic criteria for TMD will be used to assess all individuals who agree to participate. All participants will be submitted to a clinical examination and electromyographic analysis of the masseter muscles and anterior bundle of the temporal muscles bilaterally, to determine TMD. Based on the clinical findings, the participants will be classified as having or not having TMD. Those with TMD will be divided into four groups, three of which will receive low-level laser therapy and one of which will receive a placebo treatment. The treatments will involve the TMJ region alone, the masseter and temporal muscles alone, or both these regions together. The data will be submitted to descriptive statistical analysis. The chi-square test and Fisher’s exact test will be used to determine associations among the categorical variables. The Student’s *t* test and analysis of variance will be used for the comparison of mean electromyographic signals. Pearson’s correlation coefficients will be calculated for the analysis of correlations among the continuous variables.

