### Procedures

As the proposed study constitutes a randomized clinical trial, the recommendations of the Consolidated Standards of Reporting Trials (CONSORT) [26] will be followed to allow greater transparency and enhance the quality of the findings. The subjects will be allocated to five groups, as delineated in Table 1.

**Table 1 T1:** Summary of experimental conditions

**Group**	**TMD**	**Laser application site**	**Therapeutic intervention**
I	Absent	—	Control group
II	Present	TMJ	LLLT
III	Present	Muscles of mastication	LLLT
IV	Present	TMJ and muscles of mastication	LLLT
V	Present	TMJ and muscles of mastication	Placebo

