### Sample size calculation

Based on data from the literature [24], using the EMG signal of the masseter muscles, and following LLLT as the basis, with mean values of 13.4 (standard deviation: 2.8) and 11.9 (standard deviation: 1.9) individuals per group, for the experimental study and comparison of means with equal samples (hypothesis test), considering a 5% level of significance (*P* < 0.05) and 80% test power, the sample size was determined to be 15 individuals per group, using the DINAM 1.0 program [32].

Seventeen individuals will be selected for each group to compensate for possible losses.

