#### Organization and statistical treatment of data

The data will be tabulated and treated using the SPSS 12.0 program for Windows and will be submitted to descriptive statistical analysis. The chi-square test and Fisher’s exact test will be used to determine associations among the categorical variables. The Student’s *t* test for paired data will be used to analyze the averages of electromyographic and occlusal contacts before and after treatment. The Student’s *t* test and analysis of variance will be used to compare mean electromyographic signals and occlusal contacts between different groups. For data that are not normally distributed, the differences before and after treatment in the same group and between groups will also be analyzed, using the Mann–Whitney and Wilcoxon paired tests. Pearson’s correlation coefficients will be calculated for the analysis of correlations among the continuous variables. The level of significance will be set to 5% (*P* < 0.05).

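### The fallback for non-normal data names only two-group and paired rank tests, so the comparison of four TMD arms loses its only overall test

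*Protocol article*

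**What the plan says.** The Abstract of the protocol article describes four randomised arms: "Those with TMD will be divided into four groups, three of which will receive low-level laser therapy and one of which will receive a placebo". Procedures and Table 1 add a group without TMD: "The subjects will be allocated to five groups".

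The section Organization and statistical treatment of data then sets these tests for EMG and occlusal contacts:

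- Within a group, the Student's "test for paired data will be used to analyze the averages of electromyographic and occlusal contacts before and after treatment".
- Between groups: "analysis of variance will be used to compare mean electromyographic signals and occlusal contacts between different groups", alongside Student's t test.
- As the fallback: "For data that are not normally distributed, the differences before and after treatment in the same group and between groups will also be analyzed". The tests named there are Mann–Whitney, for two independent groups, and Wilcoxon, for pairs.

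The significance level is 5%. The section names no rank test for three or more groups and no adjustment for pairwise testing. It does not say which result counts if a parametric and a rank test of the same outcome disagree.

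**The concern.** A fallback should answer the same question as the test it stands in for. The paired t test has its counterpart in Wilcoxon, and the two-sample t test has its counterpart in Mann–Whitney. ANOVA has none. For a non-normal outcome, the stated plan can address the arms only two at a time, each pair at 5%.

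At stake is the chance of declaring some difference among the arms when there is none. It also matters that outcomes in the same trial could be judged by different rules: one with an overall test available, the next without.

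The wording adds two uncertainties. The ANOVA sentence speaks of mean signals, while the fallback speaks of before–after differences, so the quantity compared between groups may change with the distribution. The word *also* may mean that the rank tests are run on top of the parametric ones.

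**Working it through.** **Inputs from the article**
- Groups: five, of which four have TMD (Table 1).
- Group size: 15 by calculation, 17 recruited (Sample size calculation). These serve here only as group sizes; whether 15 follows from its own inputs is a separate matter.
- Level: 5% per test.

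The article gives no error rate over the set of comparisons, so there is no figure of its own to reproduce.

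**Assumptions**
- No true difference between any groups, independent observations and equal group sizes.
- Two-sided tests (the article does not state sidedness).
- Normal data, or lognormal data with log-SD 0.5.

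**Step 1: number of pairs.** With k groups there are k(k − 1)/2 pairs.
- Four TMD arms: 4 × 3/2 = 6.
- Five groups: 5 × 4/2 = 10.

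**Step 2: rate if the pairs were independent.** This is 1 − 0.95^m for m pairs.
- m = 6: 1 − 0.95^6 = 0.265.
- m = 10: 1 − 0.95^10 = 0.401.

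Pairs that share an arm are correlated, so these figures overstate the rate and simulation is needed.

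**Step 3: simulation, 17 per group, 4,000 null trials per row.** The entries are the proportion of trials with P < 0.05, for the overall test or for at least one pair.

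| Groups | Data | ANOVA | Kruskal–Wallis | Any Mann–Whitney pair | Any t-test pair |
|---|---|---|---|---|---|
| 4 | normal | 0.051 | 0.047 | 0.202 | 0.203 |
| 4 | lognormal | 0.049 | 0.050 | 0.206 | 0.189 |
| 5 | normal | 0.052 | 0.043 | 0.284 | 0.284 |
| 5 | lognormal | 0.046 | 0.047 | 0.285 | 0.278 |

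The simulation standard error is √(0.20 × 0.80/4000) = 0.006 for a rate near 20% and √(0.05 × 0.95/4000) = 0.003 for a rate near 5%.

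A separate run of 3,000 lognormal null trials agrees:
- Any of six Mann–Whitney pairs: 0.182 at 15 per group, 0.196 at 17.
- Any of ten pairs: 0.267 at 15 per group, 0.297 at 17.

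**Step 4: what drives the inflation.** The two pairwise columns are nearly equal. Unadjusted pairs produce the excess whether the test is t or Mann–Whitney. What the fallback removes is the one planned test that holds about 5% across all the arms.

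**Step 5: if both tests are run on one pair and either is accepted.** The same simulations give 0.059 to 0.071, that is about 6–7% in place of 5%.

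**The case against.** The strongest reply is that the parametric plan is not ANOVA alone. It also lists the t test between groups, Mann–Whitney is the proper counterpart of that test, and pairwise t tests inflate error just as much. This stands: the 20% and 28% cannot be blamed on the fallback or on ranks. It does not restore the missing overall test. With normal data the plan has an ANOVA on which to rest the conclusion across the arms; with non-normal data it has nothing equivalent.

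A second reply is that an article condenses the plan. That excuses silence, and the absence of a named normality test is no fault here. But the article does name the fallback tests, and its list does not fit a design with more than two groups.

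A third reply concerns the wording. The fallback sentence can be read as before–after differences within a group (Wilcoxon) and, separately, differences between groups (Mann–Whitney), which mirrors the two preceding sentences with no change of quantity. *Also* can simply mean that non-normal data are analysed too. Both readings are plausible, so these are ambiguities to remove and not demonstrated errors.

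A reader might go further and infer that results will hinge on an unreliable normality check in small groups. The article describes no such check, threshold or target, so any trigger rate would rest on a test and a distribution that the reader supplies. Likewise, the precision gained or lost by moving from levels to changes depends on a before–after correlation that the article does not give.

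**Conclusion.** The point holds in a limited form. As written, the plan for non-normal data has no overall test across the four TMD arms or the five groups. If its pairwise tests are used unadjusted, the chance of at least one false positive per outcome is about 20% for six pairs or 28% for ten, against 4–5% for one Kruskal–Wallis test.

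These figures assume no true differences, equal groups of 17 and two-sided tests at 5%. They changed little between the two distributions tried or at 15 per group. The six-pair figure is the more relevant, because Group I is defined by the absence of TMD and need not resemble the other groups even if the laser has no effect.

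The possible switch from levels to changes and the possible double running of tests each rest on one of two readings. If both tests are run, the added error per comparison is small (about 6–7%); the larger difficulty is that neither result is named as decisive.

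**What to change.** Replace the fallback sentence with wording to this effect:

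*Each outcome is compared across Groups II–V on one quantity fixed in advance (for example, the before–after change), whatever its distribution. Where a rank analysis is used, it is the Kruskal–Wallis test on that same quantity, and it replaces the analysis of variance. Pairwise comparisons, by t test or Mann–Whitney, are adjusted for multiplicity by Holm's method.*

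The adjustment is needed even with an overall test in front. With four arms, unadjusted pairs after a significant Kruskal–Wallis test do not control the error among the remaining arms when one arm truly differs.

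The cost is wording only; design, measurements and sample size do not change. The downside is somewhat fewer nominally significant pairwise results: with six pairs, Holm compares the smallest P value with 0.05/6 = 0.0083. No transformation need be imposed, since the article gives no evidence on the shape of the data. Recruitment is under way (Trial status), so the change should be recorded before outcome data are analysed.

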## Discussion

Signs and symptoms of TMD are found in a large portion of the population. The pain that often accompanies this condition can compromise mandibular movements and lead to a reduction in quality of life. Bad posture, malocclusion, parafunctional habits, and other clinical conditions can lead to the development of TMD, which may also be associated with psychological factors [2,4,5,8].

Orofacial pain is the most common complaint of individuals with TMD. This pain can vary from mild to extreme discomfort and may result from the increase in muscle activity [2,4,5]. Surface EMG assists in the diagnosis of TMD by allowing the assessment of muscle function and dysfunction in the resting position as well as during occlusion and mastication. Indeed, *in vivo* analysis of muscle physiology is important to the diagnosis of TMD and the monitoring of this condition throughout the therapeutic process [29].

Owing to the complexity and multifactor etiology of this TMD, a number of treatment options have been proposed, such as LLLT, acupuncture, ultrasound, massage therapy, psychological treatment, drug therapy, and the use of a bite plate [1,9,24,25]. LLLT is a low-cost, noninvasive form of treatment that offers pain relief, a reduction in inflammation and enhanced tissue regeneration [1-3,6,11,20-22]. While a number of studies report the use of LLLT for the treatment of TMD, [1-3,6,7,11-13,20-25] few papers have addressed treatment in adolescents. Thus, the investigation of the effects of LLLT in the adolescent population with TMD is of extreme importance to outlining an effective treatment protocol for pain relief and improving the quality of life of affected individuals.

## Trial status

The proposed study is currently in the recruitment phase, and individuals are being diagnosed with TMD using the RDC-TMD questionnaire.

## Abbreviations

LLLT: Low-level laser therapy; MCE: Maximum clenching effort; MI: Maximum intercuspation; RMS: Root mean square; TMD: Temporomandibular disorder; TMJ: Temporomandibular joint.
